### Blinding

This trial employs an assessor-blinded design in which outcome assessors are blinded to treatment allocation. A dedicated, unblinded intervention therapist will be responsible for delivering iTBS and configuring tSCS at each session and will have no involvement in outcome assessment. Participants in the control arm will be aware that they are not receiving iTBS, as the brief nature of the iTBS procedure and the characteristic scalp sensation make participant-level sham impractical in this pilot study. To mitigate expectation effects, both arms will be framed during consent as “active neuromodulation combined with rehabilitation” with no comparative ranking. Both groups receive identical therapist contact time, session structure, and rehabilitation content. The Credibility/Expectancy Questionnaire will be administered at baseline and week 2 and entered as a covariate in sensitivity analyses of the primary outcome. However, assessor blinding will be rigorously maintained through physical separation of intervention delivery and outcome assessment areas within the rehabilitation department. The success of assessor blinding will be formally evaluated using a blinding questionnaire at week 12 and week 24. Bang’s Blinding Index will be used, a validated metric ranging from minus 1 (opposite guessing) to +1 (complete unblinding), with 0 indicating random guessing. If Bang’s Blinding Index exceeds 0.2 with 95% CI excluding zero, a pre-planned sensitivity analysis will re-analyze the primary outcome using only objective/instrumented measures (grip/pinch dynamometry, Nine-Hole Peg Test, Box and Block Test, and neurophysiological parameters), and an independent second assessor will re-score a random 30% sample of ISNCSCI examinations from video recordings.

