### Outcome measures

#### Primary outcome

The primary outcome is the change in Upper Extremity Motor Score (UEMS) from baseline (week 0) to post-intervention (week 12). The UEMS is a component of the International Standards for Neurological Classification of Spinal Cord Injury (ISNCSCI) examination and assesses the strength of 10 key muscles of the upper extremities (5 per side) on a 0 to 5 scale, yielding a score of 0 to 25 per side or 0 to 50 bilaterally. The UEMS has well-established psychometric properties, is sensitive to change in SCI populations, and was used as a primary or secondary endpoint in the Up-LIFT trial and other major SCI neuromodulation studies (Moritz et al., 2024; Singh et al., 2024).

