### Study schedule

#### Data collection and management

The schedule of enrollment, interventions, and assessments is presented in Table 3. Clinical outcomes will be assessed by trained, certified assessors who are blinded to group allocation and have demonstrated inter-rater reliability (intraclass correlation coefficient of 0.85 or higher) on the ISNCSCI examination. All data will be collected using electronic case report forms (eCRFs) hosted on a secure REDCap database maintained by the Clinical Research & Innovation Office, Tan Tock Seng Hospital, with automated range checks, audit trails, and role-based access control. Neurophysiological data (MEPs, CMCT, EMG) will be recorded using a dedicated EMG system and processed semi-automatically with manual verification by a blinded neurophysiologist. All data will be backed up daily and stored on encrypted institutional servers in compliance with Singapore’s Personal Data Protection Act (PDPA) and the HBRA.

**TABLE 3 T3:** SPIRIT schedule of enrollment, interventions, and assessments.

Timepoint	Screen	Baseline (Wk 0)	Intervention (Wk 1-12)	Post-Tx (Wk 12)	FU1 (Wk 16)	FU2 (Wk 24)
Informed consent	X					
Eligibility assessment	X					
Medical history	X					
Surgeon clearance	X					
Randomization		X				
iTBS (experimental arm)			2x/wk			
tSCS (both arms)			2x/wk			
UL rehabilitation (both arms)			2x/wk Wk 6 Each visit			
ISNCSCI / UEMS		X		X	X	X
GRASSP-2		X		X	X	X
Grip/Pinch strength		X		X	X	X
Nine-Hole Peg Test		X		X	X	X
Box and Block Test		X		X	X	X
CUE-T		X		X	X	X
SCIM-III		X		X	X	X
Modified Tardieu Scale		X		X	X	X
CMCT and MEP assessment		X		X	X	X
EMG		X		X	X	X
EQ-5D-5L		X		X		X
Modified GAS		X		X	X	X
Adverse events				X	X	X
Blinding assessment				X		X

ISNCSCI, International Standards for Neurological Classification of Spinal Cord Injury; UEMS, Upper Extremity Motor Score; GRASSP-2, Graded Redefined Assessment of Strength, Sensibility and Prehension version 2; CUE-T, Capabilities of Upper Extremity Test; SCIM-III, Spinal Cord Independence Measure III; CMCT, central motor conduction time; MEP, motor evoked potential; EMG, electromyography; GAS, Goal Attainment Scale; FU, follow-up; Wk, week; UL, upper limb.

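### Assessor guesses at weeks 12 and 24 can beat chance because iTBS works, so the blinding trigger can report failed blinding with no allocation leak

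*Protocol article*

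**What the plan says.** The Blinding section fixes four things.

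- **Timing:** "The success of assessor blinding will be formally evaluated using a blinding questionnaire at week 12 and week 24". Table 3 agrees: its blinding row ("Blinding assessment X X") marks the post-treatment and second follow-up visits, at which ISNCSCI/UEMS and the rest of the motor battery are also done.
- **Reference value:** Bang's index runs from minus 1 to +1, "with 0 indicating random guessing".
- **Threshold:** the rule is met if the "Blinding Index exceeds 0.2 with 95% CI excluding zero".
- **Consequence:** "a pre-planned sensitivity analysis will re-analyze the primary outcome using only objective/instrumented measures", and "an independent second assessor will re-score a random 30% sample of ISNCSCI examinations from video recordings".

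The primary outcome is UEMS change from week 0 to week 12. The Hypotheses section expects at least 2 points more gain with iTBS. The article gives neither the order of guess and examination within a visit, nor whether one assessor follows a participant throughout, nor a recorded reason for the guess.

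**The concern.** An index of zero stands for intact blinding only if the guess cannot draw on the effect of treatment. Here the guess is requested when recovery may already be visible. An assessor who answers iTBS for participants who improved more will be right more often than chance whenever iTBS works, although nobody has disclosed anything. The index then registers efficacy and disclosure alike.

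The week-24 guess adds a second problem. It follows the examinations at weeks 12 and 16, so it is not evidence about how the week-12 UEMS was scored, yet the rule as worded lets either time point set off a re-analysis of that outcome.

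At stake is the credibility of the effect estimate that the pilot is meant to supply: a report that assessor blinding failed becomes more likely the better iTBS works.

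**Working it through.** The article gives no operating characteristic for the rule, so there is no stated figure to reproduce. The check asks how often the rule fires when there is no leak at all.

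**Inputs from the document:** 12 per arm, at least 10 evaluable per arm (Sample size); index above 0.2 with 95% CI excluding zero (Blinding); hypothesised effect of 2 UEMS points (Hypotheses).

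**Assumptions:** Wald interval; the index computed per arm and the rule met if either arm meets it; one time point; guesses independent between participants. The SD of UEMS change is not given, so effects are in SD units: 2 points is 1 SD if the SD is 2, 0.5 SD if it is 4, and 0.33 SD if it is 6.

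**1. The rule in counts.** With only definite guesses and a proportion p correct, the index is 2p − 1 and its SE is 2√(p(1 − p)/n).
- n = 12, 9 correct: index 0.50, SE 0.25, lower limit 0.50 − 1.96 × 0.25 = 0.01. Met.
- n = 12, 8 correct: index 0.33, SE 0.27, lower limit −0.20. Not met.
- n = 10: 8 correct are needed (index 0.60).

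**2. Random guessing.** At n = 12, P(9 or more correct | p = 0.5) = 0.073 per arm, and 1 − (1 − 0.073)² = 0.141 for either arm. This 14% is small-sample Wald error plus counting two arms. It has nothing to do with efficacy and is the baseline to compare with.

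**3. Guesses that follow visible change.** If the assessor answers iTBS when change lies above the midpoint of the two arm means, P(correct) = Φ(d/2): 0.60, 0.66 and 0.69 at d = 0.5, 0.8 and 1. The expected index is 0.20, 0.31 and 0.38 with no leak. The one-arm probabilities at n = 12 are 0.223, 0.361 and 0.466.

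**4. Weaker versions.** If only half the guesses use visible change, P(correct) is the average of Φ(d/2) and 0.5. If 25% answer that they do not know, the index is (correct − wrong)/n with the multinomial variance; this case was simulated.

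| Either arm, 12 per arm, no leak | No effect | 0.5 SD | 0.8 SD | 1 SD |
|---|---|---|---|---|
| All guesses informed and definite | 14% | 40% | 59% | 72% |
| Half informed, all definite | 14% | 25% | 33% | 39% |
| Half informed, 25% don't know | 8% | 14% | 18% | 22% |

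The share due to efficacy is the difference from the first column of the same row: at 0.5 SD, 40 − 14 = 26 percentage points in the top row and 14 − 8 = 6 in the bottom row. With 10 per arm and all guesses informed, the rates are 30%, 47% and 59%, against 11% with no effect.

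**5. A split the assessor could actually make.** Assessors cannot know the midpoint of the arm means. If they split at the pooled median instead, both arms trigger together, and the rate is 14% at 0.5 SD and 45% at 1 SD. For a 2-point effect with SD 6 it is 8%, close to the 7.3% that random guessing gives in one arm. With no effect this split gives only (220² + 66² + 12² + 1)/2,704,156 = 2.0%, so a small excess remains within that model.

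**6. One arm read alone.** If assessors answer iTBS for 75% of all participants regardless of arm, the iTBS arm has p = 0.75 and P(9 or more of 12) = 65%. This is separate from timing, but it is why the two arms' indices should be read together.

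**The case against.** The strongest reply is that the trigger only screens. It adds a sensitivity analysis on instrumented measures and an independent partial re-score, and those checks could support a real effect after a false alarm. This stands. A reader might infer that a triggered rule replaces the primary analysis, or that a true benefit would be written off as assessor bias. The document supports neither: the Statistical analysis section keeps the mixed model for the primary outcome and reports all efficacy comparisons as exploratory.

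A second reply is that the article names the visit and not the order within it, so the week-12 guess might precede the examination. This also stands, and it weakens the week-12 part. It does not help week 24, when two post-treatment examinations have already taken place. How much change one assessor can see also depends on whether that assessor examined the participant before, which is not stated.

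A third reply is that the larger percentages come from a favourable model: every guess definite, every guess driven by outcome, and a split at a midpoint nobody knows. Both arms also receive active tSCS and rehabilitation. This is fair, so only the range should be quoted.

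Finally, it is tempting to conclude that the guess should simply move to before the week-12 examination. Participants know their arm, so the examination itself is a likely route of disclosure, and a guess taken beforehand would miss it.

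**Conclusion.** The point holds in a limited form. As written, the rule reads above-chance guessing as failed blinding at times when the guess can reflect treatment response, and it lets a week-24 guess bear on a week-12 score. The consequence is a false report of failed blinding plus an unneeded sensitivity analysis and re-score, more likely when iTBS works. The primary analysis is not altered.

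With 12 per arm, no leak, one time point and either arm counted, the rule fires in about 14% to 40% of trials at 0.5 SD and 22% to 72% at 1 SD, against 8% to 14% with no effect. The lower ends assume half the guesses informed and 25% don't-know answers; the upper ends assume all guesses informed and definite. With a pooled-median split and a small effect, the rate is hardly different from random guessing in one arm. These figures rest on an SD that the document does not give and on assumed guessing behaviour. That the index cannot separate efficacy from disclosure rests on neither.

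**What to change.** In the Blinding section and Table 3:

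1. Base the trigger for the week-12 primary on the week-12 guess only.
2. Record the reason with each guess: disclosure or seen contact, perceived improvement, or pure guess.
3. Have assessors log any disclosure when it happens.
4. Act on guesses attributed to disclosure and on logged disclosures, reading the two arms' indices together.
5. Report improvement-based guesses and the week-24 index descriptively.

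A guess just before the week-12 examination may be added, but should not be the only trigger.

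The cost is one added form item, a log and a change of wording, with no extra visits or staff. The article reports no participants enrolled when it was prepared. The drawback is reliance on assessors' own account of why they guessed as they did.

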### Interventions

#### Overview

Both arms will receive individualized tSCS combined with standardized upper limb rehabilitation. The experimental arm will additionally receive iTBS immediately prior to each rehabilitation session. Interventions will be delivered twice per week for 12 weeks, yielding a total of 24 sessions. A minimum of 20 completed sessions (83%) will be required for per-protocol analysis.

#### Transcutaneous spinal cord stimulation protocol (both arms)

Individualized tSCS will be delivered using a programmable constant-current stimulator (DS8R, Digitimer, UK, or equivalent) with 5 × 10 cm self-adhesive PALS electrodes (Axelgaard, USA) via adhesive electrodes placed over the posterior midline of the cervical spine at the spinous process interspaces one level above and below the participant’s injury level (typically C3-C4 and/or C6-C7), targeting the dorsal roots corresponding to the upper limb motor pools (C5 to T1). This placement aligns with segment-specific dorsal root activation demonstrated by Sayenko et al. (2015) and the cervical programming recommendations of Gelenitis et al. (2025). Reference electrodes will be placed bilaterally over the anterior superior iliac spines (ASIS) or clavicles, selected based on individual tolerance and response (Gelenitis et al., 2025). Stimulation parameters will be as follows: biphasic rectangular pulses at 30 Hz burst frequency, each 1 ms pulse filled with a 10 kHz carrier frequency, intensity individualized between 40 and 120 mA. The 10 kHz carrier reduces cutaneous nociceptor activation and permits the higher intensities required for deep dorsal root activation at cervical levels. These parameters are consistent with those employed in the Up-LIFT trial and the published programming recommendations (Gelenitis et al., 2025; Moritz et al., 2024). Intensities up to 120 mA at the cervical level have been demonstrated as safe and tolerable in Up-LIFT (Moritz et al., 2024) and Gelenitis et al. (2025) when delivered with a 10 kHz carrier; cardiovascular safety at this intensity range was confirmed in Samejima et al. (2025). Stimulation will be delivered continuously during the rehabilitation session (approximately 45 min). Titration algorithm: (1) verify electrode placement and skin impedance; (2) ramp intensity in 5 mA increments from 20 mA; (3) identify motor response threshold (visible or palpable muscle activation); (4) set therapeutic intensity at 80–90% of tolerance threshold or intensity eliciting motor facilitation without discomfort; (5) re-titrate every 4 sessions to account for habituation.

#### Intermittent theta burst stimulation protocol (experimental arm only)

iTBS will be delivered before each tSCS and rehabilitation session using a figure-of-eight coil connected to a biphasic magnetic stimulator (MagPro X100 with MC-B70 figure-of-eight coil, MagVenture, Denmark, or equivalent). The coil will be positioned over the hand representation area of the primary motor cortex (M1) contralateral to the more impaired upper limb. The motor hotspot will be determined as the scalp location yielding the largest and most consistent motor evoked potentials (MEPs) in the first dorsal interosseous (FDI) or abductor pollicis brevis (APB) muscle. The active motor threshold (AMT) will be determined using the relative frequency method as the minimum stimulator intensity eliciting discernible MEPs in at least 5 of 10 consecutive trials during slight voluntary contraction (approximately 10% of maximum).

The iTBS protocol will consist of bursts of 3 magnetic pulses delivered at 50 Hz, repeated at a theta frequency of 5 Hz, with 2-s trains repeated every 10 s for 20 repetitions, delivering a total of 600 pulses per session (Huang et al., 2005). Stimulation intensity will be set at 80% of AMT. Each iTBS session will last approximately 3–4 min and will be completed before electrode placement and tSCS activation. These parameters are consistent with established international safety guidelines for rTMS (Lefaucheur et al., 2020; Rossini et al., 2015) and with the iTBS protocols employed in recent SCI studies (Feng et al., 2023; Patel et al., 2025; Shi et al., 2026).

#### Standardized upper limb rehabilitation (both arms)

All participants will receive individualized, standardized upper limb rehabilitation during each session, commencing after iTBS delivery (in the experimental arm) and continuing throughout tSCS application. The rehabilitation program is based on the functional task practice protocol employed in the Up-LIFT trial (Moritz et al., 2024) and will be prescribed and supervised by a qualified physiotherapist and occupational therapist at Alexandra Hospital. Each session will comprise approximately 45–60 min of structured UE exercises, including the following components: (1) upper limb ergometry and gross UE movements (reaching, overhead press); (2) isolated finger movements and fine motor tasks; (3) simple and complex pinch tasks using graded objects; (4) grip strength training; (5) bimanual coordination tasks; and (6) individualized functional activities prescribed by the attending occupational therapist based on their clinical assessment. Task difficulty will be adjusted according to the participant’s functional capacity using a standardized progression algorithm.

#### Treatment session sequence

Each session in the experimental arm will follow the sequence: (1) iTBS over M1 (approximately 3–4 min); (2) tSCS electrode placement and activation (approximately 5 min setup); (3) combined tSCS plus upper limb rehabilitation (approximately 45–60 min). Total session duration for the experimental arm is approximately 55–70 min. The control arm follows the same sequence without the iTBS component, with total session duration of approximately 50–65 min.

### Outcome measures

#### Primary outcome

The primary outcome is the change in Upper Extremity Motor Score (UEMS) from baseline (week 0) to post-intervention (week 12). The UEMS is a component of the International Standards for Neurological Classification of Spinal Cord Injury (ISNCSCI) examination and assesses the strength of 10 key muscles of the upper extremities (5 per side) on a 0 to 5 scale, yielding a score of 0 to 25 per side or 0 to 50 bilaterally. The UEMS has well-established psychometric properties, is sensitive to change in SCI populations, and was used as a primary or secondary endpoint in the Up-LIFT trial and other major SCI neuromodulation studies (Moritz et al., 2024; Singh et al., 2024).

#### Secondary outcomes

Secondary clinical and neurophysiological outcomes are summarized in Table 2.

**TABLE 2 T2:** Secondary outcome measures.

Outcome measure	Description	Domain	Timepoints
GRASSP-2	Graded Redefined Assessment of Strength, Sensibility and Prehension version 2; comprehensive UE impairment measure for tetraplegia	Motor/Sensory	Wk 0, 12, 16, 24
Grip/pinch strength	Maximal grip force (Jamar dynamometer), lateral pinch, tip pinch, and tripod pinch (pinch gauge)	Motor	Wk 0, 12, 16, 24
Nine-Hole Peg Test	Timed fine motor dexterity assessment	Fine Motor	Wk 0, 12, 16, 24
Box and Block Test	Gross manual dexterity (blocks transferred in 60 s)	Gross Motor	Wk 0, 12, 16, 24
CUE-T	Capabilities of Upper Extremity Test; objective functional assessment for tetraplegia	Function	Wk 0, 12, 16, 24
SCIM-III	Spinal Cord Independence Measure III; self-care, respiration, sphincter management, mobility	Independence	Wk 0, 12, 16, 24
Modified Tardieu Scale	Velocity-dependent spasticity of elbow and wrist flexors/extensors	Spasticity	Wk 0, 6, 12, 16, 24
CMCT	CMCT per IFCN guidelines: CMCT = MEP latency minus PCT, where PCT = (F-latency + M-latency minus 1) / 2	Neurophysiology	Wk 0, 12, 16, 24
MEP parameters	Amplitude, latency, resting and active motor thresholds from FDI and APB	Neurophysiology	Wk 0, 12, 16, 24
EMG	Surface electromyography from key upper limb muscles during standardized tasks	Neurophysiology	Wk 0, 12, 16, 24
EQs-5D-5L	Generic health-related quality of life; utility index and visual analog scale	Quality of Life	Wk 0, 12, 24
Modified GAS	Patient-identified goals scored on a standardized attainment scale	Patient-Centered	Wk 0, 12, 16, 24
Adverse events	Structured adverse event recording at every session	Safety	Every session

GRASSP-2, Graded Redefined Assessment of Strength, Sensibility and Prehension version 2; CUE-T, Capabilities of Upper Extremity Test; SCIM-III, Spinal Cord Independence Measure III; CMCT, central motor conduction time; MEP, motor evoked potential; FDI, first dorsal interosseous; APB, abductor pollicis brevis; EMG, electromyography; GAS, Goal Attainment Scale; Wk, week.

##### Feasibility outcomes

As this is a pilot study, pre-specified feasibility outcomes will be evaluated against the following progression criteria: (1) recruitment rate of at least 2 participants per month; (2) retention rate of 80% or higher (i.e., at least 20 of 24 participants completing the study); (3) intervention adherence of 83% or higher (i.e., at least 20 of 24 sessions completed); (4) assessment completion rate of 90% or higher for the primary outcome; and (5) no serious adverse events attributable to the combined intervention. These criteria will determine whether progression to a full-scale confirmatory trial is warranted.

### Study schedule

#### Data collection and management

The schedule of enrollment, interventions, and assessments is presented in Table 3. Clinical outcomes will be assessed by trained, certified assessors who are blinded to group allocation and have demonstrated inter-rater reliability (intraclass correlation coefficient of 0.85 or higher) on the ISNCSCI examination. All data will be collected using electronic case report forms (eCRFs) hosted on a secure REDCap database maintained by the Clinical Research & Innovation Office, Tan Tock Seng Hospital, with automated range checks, audit trails, and role-based access control. Neurophysiological data (MEPs, CMCT, EMG) will be recorded using a dedicated EMG system and processed semi-automatically with manual verification by a blinded neurophysiologist. All data will be backed up daily and stored on encrypted institutional servers in compliance with Singapore’s Personal Data Protection Act (PDPA) and the HBRA.

**TABLE 3 T3:** SPIRIT schedule of enrollment, interventions, and assessments.

Timepoint	Screen	Baseline (Wk 0)	Intervention (Wk 1-12)	Post-Tx (Wk 12)	FU1 (Wk 16)	FU2 (Wk 24)
Informed consent	X					
Eligibility assessment	X					
Medical history	X					
Surgeon clearance	X					
Randomization		X				
iTBS (experimental arm)			2x/wk			
tSCS (both arms)			2x/wk			
UL rehabilitation (both arms)			2x/wk Wk 6 Each visit			
ISNCSCI / UEMS		X		X	X	X
GRASSP-2		X		X	X	X
Grip/Pinch strength		X		X	X	X
Nine-Hole Peg Test		X		X	X	X
Box and Block Test		X		X	X	X
CUE-T		X		X	X	X
SCIM-III		X		X	X	X
Modified Tardieu Scale		X		X	X	X
CMCT and MEP assessment		X		X	X	X
EMG		X		X	X	X
EQ-5D-5L		X		X		X
Modified GAS		X		X	X	X
Adverse events				X	X	X
Blinding assessment				X		X

ISNCSCI, International Standards for Neurological Classification of Spinal Cord Injury; UEMS, Upper Extremity Motor Score; GRASSP-2, Graded Redefined Assessment of Strength, Sensibility and Prehension version 2; CUE-T, Capabilities of Upper Extremity Test; SCIM-III, Spinal Cord Independence Measure III; CMCT, central motor conduction time; MEP, motor evoked potential; EMG, electromyography; GAS, Goal Attainment Scale; FU, follow-up; Wk, week; UL, upper limb.

